### **b. Institutional and procedural criteria**

Indicators of institutions and procedures will be systematically collected and will concern human resources, institutional resources, the actual number of directives filled in, the number of people who had recourse to a peer-worker, the number of contacts with the peer-worker required to fill in the document, the number of shared directives and with which actor(s), use of the document in case of hospitalization, anticipated directives respected or not in the case of hospitalization, the number and type of collaborative link with local partners, description of the actions performed by the peer-worker, etc. Identification of future dysfunctions, their origins and the corrective measures applied.

## **3. Data collection periods**

Individual case report forms have been developed especially for this trial; they are articulated around the three assessment periods described in the following chapter: initial assessment and follow-up visits at 6 and 12 months.

Data will be collected at a place of the patient's choice.

Data will be manually entered into a laptop dedicated to this use, using software specifically developed for the trial.

The following table summarizes the contents and the frequency of assessments for the two groups of subjects included in the trial.

|                                                                            | Eligibility
Inclusion
Init. Ass. | 6 months | 12 months |
|----------------------------------------------------------------------------|----------------------------------------|----------|-----------|
| Informed consent, check inclusion/exclusion criteria:                      |                                        |          |           |
| admissibility questionnaire                                                | x                               |          |           |
| Sociodemographic characteristics                                           | x                               |          |           |
| Anamnestic data & personal medical history                                 | x                               |          |           |
| Data related to mental health:                                             |                                        |          |           |
| CGI                                                                        | x                               |          | x  |
| Recovery: RAS                                                              | x                               | x | x  |
| Therapeutic alliance: 4-PAS                                                | x                               | x | x  |
| Insight: SUMS                                                              | x                               | x | x  |
| Empowerment: ES                                                            | x                               | x | x  |
| Quality of life: S-QOL                                                     | x                               | x | x  |
| Satisfaction CSQ-8                                                         | x                               | x | x  |
| Data related to recourse to care system                                    | x                               | x | x  |
| Data related to indicators of institution and processes, lost to follow-up | x                               | x | x  |

## **B. Procedure**

|                                                                                                                                                                                                                                                                                                                                                                                                                                                                                                                                                                                                                                                                                                                                                                                                                                                                                                                                                                                                                                                                                                                                                                                                                                                                                                                                                                                                                  | When?    | Who?                       | Interviewers Y/N |
|------------------------------------------------------------------------------------------------------------------------------------------------------------------------------------------------------------------------------------------------------------------------------------------------------------------------------------------------------------------------------------------------------------------------------------------------------------------------------------------------------------------------------------------------------------------------------------------------------------------------------------------------------------------------------------------------------------------------------------------------------------------------------------------------------------------------------------------------------------------------------------------------------------------------------------------------------------------------------------------------------------------------------------------------------------------------------------------------------------------------------------------------------------------------------------------------------------------------------------------------------------------------------------------------------------------------------------------------------------------------------------------------------------------|----------|----------------------------|------------------|
| 
1. Detection – Eligibility
 
The psychiatrist investigators in charge of detecting subjects in their active file of patients will be given precise information about the trial before the recruitment period.
 
These psychiatrists are in charge of checking that the patient does meet the psychiatric inclusion criteria for the trial and of giving the type of diagnosis: schizophrenia, bipolar-I disorder, schizoaffective disorders.
 
During a meeting with a potentially eligible patient, the psychiatrist fills out the eligibility questionnaire, then once all of the eligibility criteria have been validated he/she contacts the research team investigator and faxes the filled out form serving as a "request for inclusion".
 
The psychiatrist is in charge of giving the patient information about the "DaiP" intervention and its objectives. He/she hands the patient the information sheet and then goes over the assessment goals for the "DaiP" intervention, the procedure, the advantages and the constraints.
 
An appointment is made in the next few days for a meeting between the psychiatrist investigator, the patient and the interviewer.
                                                                                                                                                                                     | D0       | Psychiatrist investigators | N                |
| 
2. Inclusion
 
The subject is recruited during this meeting.
 
If the patient is under legal protection, the legal representative is informed.
 
The interviewer and the psychiatrist make sure that the person has correctly understood and obtain his/her informed consent, or that of the legal representative where appropriate, after agreement by the patient.
 
The subject can be allowed a reflection period of one month maximum before giving consent to participate in the trial and in this case a second appointment is made.
 
Next patients are randomized. The patient is informed of their inclusion in the "PAD" or "Usual Care" arm of the trial.
 
 
• If the person is included in the "PAD" arm, the physician investigator immediately offers a meeting with the peer-worker. The interviewer makes the next appointment and takes the person's contact details. The referring psychiatrist, investigator, is in charge of informing the person's family doctor and the actors involved in care that the person will be participating in this research trial. This information is sent by post, and may enclose the sheet given in Annex 6.
 
• If the person is included in the "usual care" arm, the interviewer makes the next appointment and takes the person's contact details.
 
 | D0 to D5 |                            | Y                |

|                                                                                                                                                                                                                                                                                                                                                                                                                                                                                                                                                                                                         |           |  |        |
|---------------------------------------------------------------------------------------------------------------------------------------------------------------------------------------------------------------------------------------------------------------------------------------------------------------------------------------------------------------------------------------------------------------------------------------------------------------------------------------------------------------------------------------------------------------------------------------------------------|-----------|--|--------|
| 
3. Initial assessment
 
The interviewer fills in the sections of the case report form corresponding to initial assessment. A calendar is defined between the patient and the interviewer to plan the meetings required for the trial. The interviewer must again go over all the possible means of contact (phone if possible) for appointment reminders.
 
The assessment must be done soon after inclusion within a maximum of one month after inclusion and before the intervention starts.
                                                             | D0 to D30 |  | Y      |
| 
4. Follow-up
 
Follow-up visits take place 6 and 12 months after inclusion in the trial which formally corresponds to the date the informed consent form was signed. Follow-up assessments will be valid if their dates are within a period of +/- 30 days of the scheduled date.
 
According to the means defined with the patient, the interviewer will contact the patient before the follow-up visit, then go to the scheduled meeting at a place that suits the patient. At each visit the interviewer fills in the corresponding sections of the case report form.
 | M6
M12 |  | Y
Y |

## ***C. Number of subjects necessary and feasibility***

### **1. Number of subjects necessary**

Subjects included in the trial are people who were involuntarily admitted to hospital within the previous 12 months. According to data in French literature, the rate of involuntary hospital admission for patients suffering from psychotic disorders is 42.6% within 12 months after their previous admission(27).

Reducing these involuntary admissions by one third, i.e. 33%, would be a very significant reduction in terms of efficiency. This is a realistic hypothesis in the light of the most recent meta-analyses (59). We consider that 10% of participants will not reach experimental intervention and we estimate a 30% size effect. With these hypotheses, for an alpha risk of 2.5% (one-sided test) and 80% power, 182 subjects per group would be necessary. Over a 12-month period rate of lost to follow-up equal to 10% has been considered acceptable by the investigators involved in this project, especially with regards to the means scheduled to limit the number of people lost from sight.

Accordingly, the total number of subjects to include is 400 patients.

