### 1.1 “Psychiatric advance directives”

“Psychiatric advance directives” specify certain aspects of treatment that the person wishes (53). A physician can confirm in writing that the person had full capacity of discernment at the time it was written. When a facilitator can be present, 61% of people write the document, versus 3% with no facilitator(54).

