## IV. Care strategies under study

### A. *Pw-PAD intervention*

#### 1. Description of the contents and procedure

A person included in the pw-PAD group is incited to fill in the DaiP document "Psychiatric Advance Directives", of which they are immediately given a copy. This document is provided in Annex 5. The person is incited to meet a peer-worker to help them to write it. A peer-worker is called immediately to quickly arrange a meeting, at a place the person has chosen, preferentially in town, outside the hospital.

The person can decide to fill out the document without the help offered.

The person is encouraged to share the filled-in document: with their healthcare agent, as well as with their referring psychiatrist, study investigator, and to give them a copy. A consultation concerning the sharing of this document will be proposed and organized by the peer-worker.

In case of psychiatric hospital admission, the patient hands the document "Psychiatric Advance Directives" to the hospital team, their healthcare agent or referring psychiatrist, so as to influence the therapy given.

PAD incite to follow the preference and choices of the people in question, but the carers are not legally bound to provide the care requested if it does not correspond to practice standards.

PAD do not have any binding value for relatives and carers.

Following inclusion, if the person chooses not to benefit from the intervention, they will be recontacted by the interviewer by phone, taking care not to be too insistent so as not to compromise any future participation. The reminder can be given by the psychiatrist at their next consultation, where the document will be given again, and the peer-worker will again be contacted if the person would like help filling it in.

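### The sample-size section assumes, without a basis or a definition, that 90% of the PAD arm reaches the intervention; its own dilution step gives about 39% to 71% power over 61% to 90% uptake, not 80%

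*Combined protocol and SAP*

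**What the plan says.** Protocol VI.C.1 (Number of subjects necessary) starts from a control rate: "the rate of involuntary hospital admission for patients suffering from psychotic disorders is 42.6% within 12 months after their previous admission". It then sets the target: "Reducing these involuntary admissions by one third, i.e. 33%, would be a very significant reduction in terms of efficiency". Next comes the allowance for non-uptake: "We consider that 10% of participants will not reach experimental intervention and we estimate a 30% size effect". The result is "for an alpha risk of 2.5% (one-sided test) and 80% power, 182 subjects per group would be necessary". On attrition, a "rate of lost to follow-up equal to 10% has been considered acceptable", and "the total number of subjects to include is 400 patients".

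On uptake, protocol I.E.1.1 cites one study result: "When a facilitator can be present, 61% of people write the document, versus 3% with no facilitator". The intervention in IV.A.1 is a voluntary offer. The patient may decline it, and "The person can decide to fill out the document without the help offered". IV.A.2 leaves the number of peer-worker meetings to the patient's choices and capacities. IV.A.1 also provides for a telephone recontact and a further reminder from the psychiatrist for those who do not take up the offer.

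SAP VI.E.2.1 sets an unadjusted ITT analysis as primary, with per-protocol analyses as complementary.

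**The concern.** The step from one third to 30% only works if 90% of the PAD arm is exposed. No section gives a source for 90%. Nor does any section say whether reaching the intervention means receiving the blank document, meeting the peer-worker, completing a directive or sharing it. The one study figure on completion with a facilitator is well below 90%.

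In an ITT comparison, non-uptake shrinks the contrast directly. The protocol recognises this when it discusses earlier work: in I.E.2.1 it qualifies a trial with no difference (19% versus 21%) by noting that few participants had completed the document. The same reasoning is not carried through to this trial's own power. If uptake is lower than assumed, a null result could be read as evidence against the directives when the trial had limited power to detect the diluted effect.

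**Working it through.** **Inputs.** Control rate p1 = 0.426, relative reduction one third (33%), non-reach 10%, one-sided α = 0.025, power 80%, 182 per group, 10% loss, 400 in total (all VI.C.1). Allocation is taken as 1:1. Loss of 10% leaves 400 × 0.9 / 2 = 180 evaluable per arm.

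**Step 1: reproduce 182 per group.** Two-proportion formula, pooled variance under the null:

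n = [1.960·√(2p̄(1−p̄)) + 0.842·√(p1(1−p1) + p2(1−p2))]² / (p1 − p2)², where p̄ is the mean of p1 and p2.

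- Stated 30% effect: p2 = 0.426 × 0.70 = 0.298, n = 221 per group. Other usual forms give 219 (unpooled), 221 (arcsine) and 237 (continuity-corrected).
- Undiluted 33%: p2 = 0.426 × 0.67 = 0.285, n = 181 per group. With exactly one third, n = 178.

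So 182 matches the undiluted effect. The 10% non-reach appears in the text but apparently not in the number, so N holds no reserve for lower uptake.

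**Step 2: the plan's own dilution.** ITT reduction = one third × uptake. At 90% uptake this returns the plan's 30%.

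**Step 3: power.** Power = Φ{[(p1 − p2)√n − 1.960·√(2p̄(1−p̄))] / √(p1(1−p1) + p2(1−p2))}.

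| Uptake | ITT reduction | p2 | Power, 180 per arm | Power, 200 per arm (no loss) |
|---|---|---|---|---|
| 90% | 30.0% | 29.8% | 71% | 76% |
| 75% | 25.0% | 32.0% | 55% | 60% |
| 61% | 20.3% | 33.9% | 39% | 43% |

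For the last row: 0.426 × (1 − 0.333 × 0.61) = 0.339, a difference of 8.7 percentage points against 12.8 at 90% uptake.

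With full uptake and 180 per arm, power is 81% for one third and 80% for 33%. The stated 80% therefore corresponds to essentially full exposure.

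**The case against.** A reader might infer that only about two thirds of the planned intervention will be delivered (0.61/0.90 = 0.68), that the true effect will therefore be 20%, and that 39% should replace 10% as the non-reach figure. The documents do not support that, for four reasons.

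- **Unlike quantities.** The 61% counts people who wrote a document in another study, whereas the plan's reach is undefined. This trial adds peer-workers, reminders (IV.A.1) and a research assistant who encourages the meeting (Annex 4). Uptake could exceed 61%.
- **Another figure in the text.** VIII.D.2 expects 50 people in each city to complete the document. Over three cities that is 150 of 200, or 75%. Elsewhere, however, the protocol speaks of four sites (qualitative section), and 4 × 50 = 200 would be the whole PAD arm. The same paragraph gives a 6-month inclusion window against 12 months in VI.C.2.1. The figure is too weak to settle uptake.
- **The dilution itself is open to doubt.** The source cited for one third is reported in I.E.2.1 by group: 13% versus 27%, a reduction of 1 − 13/27 = 52%. If that is an arm-level result, non-uptake is already in it and no further dilution is due. Even 52% × 0.61 is about 32%, above the planned 30%.
- **Uptake is recorded.** VI.A.2.2(b) counts directives completed, peer-worker use and sharing, and the SAP adds per-protocol analyses.

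These points rule out treating 61% as a forecast. They do not supply a basis for 90% or restore 80% power at the stated 30% effect. The per-protocol analysis is only a partial answer, because completers select themselves and completion is not defined.

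**Conclusion.** The point holds as one about an unsupported planning assumption and an overstated power. Over 61% to 90% uptake, VI.C.1's own logic gives an ITT reduction of about 20% to 30%. Power is about 39% to 71% with 10% loss, or 43% to 76% with none. Even at the plan's own 90%, power falls short of 80%, because 182 per group was evidently not computed from the 30% effect. That part of the shortfall does not come from low uptake.

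The range rests on three assumptions: one third is the effect in those who take up the intervention, non-takers gain nothing, and controls have no uptake. The documents state none of them outright, although the plan's 10% step implies the first two. If one third is instead an arm-level effect, the 10% step is the error and 182 per group is consistent with 33%. Either way the paragraph needs correcting.

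**What to change.** In VI.C.1:

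1. Define reach, for example as a completed directive or a meeting with the peer-worker.
2. Choose one of two routes. (a) Keep the dilution and replace the single 80% with the expected ITT effect and power for 400 patients over 61% to 90% uptake: about 39% to 71% with 10% loss, 43% to 76% with no loss. (b) State, with reasons, that one third is already an ITT effect and delete the 10% step, so that 182 per group matches 33%.
3. Add there or in the SAP that a null ITT result will be read alongside the uptake counts collected under VI.A.2.2(b).

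No change in sample size is proposed. The cost is a few sentences and, under route (a), a less favourable stated power. Route (b) keeps the 80% but obliges the authors to defend one third as an effect that already includes non-uptake.

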#### 2. Description of the frequency

The number and the frequency of the meetings with the peer-worker facilitator necessary to fill in the document "Psychiatric Advance Directives" will comply as much as possible with the person's choices and the capacities.

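### The stated 80% power does not hold at the plan's own 30% effect (about 71% with 360 evaluable patients), and the sizing does not say whether that effect allows for delay before a directive exists

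*Combined protocol and SAP*

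**What the plan says.** Section VI.C.1 takes a 12-month control rate of 42.6% and sets the target: "Reducing these involuntary admissions by one third, i.e. 33%, would be a very significant reduction in terms of efficiency". It then allows for non-receipt: "We consider that 10% of participants will not reach experimental intervention and we estimate a 30% size effect". On these hypotheses it concludes: "for an alpha risk of 2.5% (one-sided test) and 80% power, 182 subjects per group would be necessary". A 10% loss to follow-up brings the total to 400. Delay is not mentioned.

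The timetable is spread over several sections:

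- **Follow-up (VI.B.4).** The 6- and 12-month visits are timed from inclusion "in the trial which formally corresponds to the date the informed consent form was signed".
- **Baseline (VI.B.3).** The assessment should come soon after inclusion, at most "one month after inclusion and before the intervention starts".
- **Start of the intervention (IV.A.1 and VI.B.2).** The patient is handed the document at once. "A peer-worker is called immediately to quickly arrange a meeting", and the inclusion step, dated D0 to D5, likewise has the meeting offered straight away.
- **Pace (IV.A.2).** The number and frequency of peer-worker meetings "will comply as much as possible with the person's choices and the capacities". No completion date is set.
- **Endpoint (VI.A.2.1).** The rate of involuntary admission is taken over 12 months, with no start date.
- **Analysis (VI.E.2.1).** The primary analysis is by intention to treat.

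**The concern.** Two separate questions arise from the same sentence of VI.C.1.

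The first is whether the sample size was calculated for the effect the section ends up assuming. The text reduces one third to 30% for the 10% not reached, then gives a number per group. If that number belongs to the undiluted effect, the allowance for non-receipt was described but never applied, and the power claim is too high.

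The second is time. An admission that occurs before a directive exists cannot be averted by it, yet under intention to treat it counts in the intervention arm. This affects patients who do complete a directive, so it is distinct from the 10% who never receive the intervention. VI.C.1 does not say whether its effect already absorbs this delay.

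In both cases, a null result would be read as stronger evidence against the intervention than the design can supply.

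**Working it through.** **Inputs.** From VI.C.1: control risk p1 = 0.426, reduction 33% or 30%, one-sided alpha 2.5%, power 80%, 182 per group, 10% loss, total 400. Equal allocation is inferred from the figure per group. Evaluable patients: 400 × 0.9 = 360, or 180 per group.

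**Formula.** Two proportions, pooled variance under the null, no continuity correction, with p̄ = (p1 + p2)/2:

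n = [1.96·√(2p̄(1−p̄)) + 0.8416·√(p1(1−p1) + p2(1−p2))]² / (p1 − p2)²

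**Step 1: reproduce 182.** With the undiluted 33%, p2 = 0.426 × 0.67 = 0.2854 and p1 − p2 = 0.1406.

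n = (1.96 × 0.6770 + 0.8416 × 0.6697)² / 0.1406² ≈ 181 per group.

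This matches 182. For the total, 364 × 1.1 = 400.4.

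**Step 2: use the stated 30%.** The dilution is 1/3 × 0.9 = 30%. Then p2 = 0.426 × 0.70 = 0.2982 and p1 − p2 = 0.1278.

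n = (1.96 × 0.6797 + 0.8416 × 0.6737)² / 0.1278² ≈ 221 per group.

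Other conventions do not recover 182: 219 with unpooled variance, 237 with continuity correction, and 174 if alpha were one-sided 5%.

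**Step 3: power at the 30% effect.** Power = Φ{[0.1278·√n − 1.96 × 0.6797] / 0.6737}.

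- n = 180: Φ(0.568) = 71.5%
- n = 182: Φ(0.582) = 72.0%

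**Step 4: delay, as a conditional calculation.** Assumptions that the documents do not supply: constant hazard, no effect before the delay d ends, the full effect afterwards, the same delay for every intervention patient, and the planned reduction taken as one for 12 months of full exposure.

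- Control hazard: −ln(1 − 0.426)/12 = 0.0463 per month.
- Intervention hazard: −ln(1 − 0.284)/12 = 0.0278 (one third), or −ln(1 − 0.2982)/12 = 0.0295 (30%).
- Intervention-arm risk: 1 − exp[−0.0463·d − λe·(12 − d)].

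Results at 180 per group (one week = 0.25 month, two weeks = 0.5 month):

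| Delay | From one third: risk, power | From 30%: risk, power | Points lost |
|---|---|---|---|
| none | 28.4%, 80.6% | 29.8%, 71.5% | – |
| 1 week | 28.7%, 78.7% | 30.1%, 69.4% | about 2 |
| 2 weeks | 29.1%, 76.6% | 30.4%, 67.2% | about 4 |
| 1 month | 29.7%, 72.3% | 31.0%, 62.8% | 8 to 9 |

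Two other ways of modelling the delay were tried at one month: scaling the reduction by 11/12, and applying the reduction only to events after the delay. Across these and the constant-hazard model, the loss runs from 7.5 to about 10 points. One month is the limit that VI.B.3 sets for the baseline assessment. The documents give no figure for writing and sharing time.

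**The case against.** On the sample size, one could say that 182 was meant for the 33% target. That agrees with the arithmetic but leaves the 10% non-receipt unallowed for, and the text places the 30% effect among the hypotheses behind 182. One could also say that admissions checked against the PMSI may be known even for patients lost to the interviewer. With all 400 counted (200 per group), power at 30% is 76.0%, still short of 80%.

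On delay, the other side is stronger, and much of it stands:

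- A reader might infer that VI.C.1 assumes twelve full months of exposure. It never says so. Diluting for patients not reached does not imply that the rest are exposed from day 0. The cited support is a trial reported at 12 months (13% against 27% in section I.E.2.1, a relative reduction of 14/27 = 52%), which may already contain set-up time. If it does, charging for delay again would double count.
- The 30 days are a ceiling. The assessment is meant to happen soon after inclusion, the document is handed over at once, and the patient may complete it alone. One to two weeks costs 2 to 4 points. Slow writing, or admissions clustered early, would raise the loss, but the documents give no figures for either.
- Offering or arranging a meeting is scheduling and can fit a same-visit baseline. The sharper tension is the immediate handover of the document.
- Counting from consent is an inference from the visit schedule, because the endpoint definition has no start date.

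**Conclusion.** The shortfall at the plan's own effect is firm. It uses only figures in VI.C.1 and a standard formula: 182 per group matches 33%, the 30% effect needs 221, and power at 180 to 182 is about 71 to 72%.

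The missing statement on delay is also a fact of the text, but its cost is conditional. With a full-exposure effect and constant hazard, it is a further 2, 4 or 8 to 9 points for one week, two weeks or one month. It is less, or nothing, if the effect already includes set-up time.

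A reader might combine the two and conclude that the trial's power is about 63%, or about 54% with a two-month delay. The documents do not support either as a single figure. Each adds a uniform delay that the plan does not predict to the separate mismatch between 33% and 30%, which alone accounts for about 9 points of the fall from 80%.

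The timing instructions need reconciling whatever model is used: the document is handed over immediately, yet a baseline that may be as late as day 30 must come before the intervention.

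**What to change.** 1. **VI.C.1, power.** Replace 80% with about 71% for the 30% effect at 360 evaluable patients. Keeping 80% would instead take about 492 patients (2 × 221 / 0.9).
2. **VI.C.1, delay.** State whether the assumed 12-month effect includes the time to set up a directive. If not, report the loss separately as a conditional range (2, 4 or 8 to 9 points for one week, two weeks or one month), with its assumptions.
3. **VI.A.2.1 and VI.E.2.1.** State that the 12 months run from consent or randomisation, the same in both arms, and keep the intention-to-treat count from that date. Do not start the count at completion of the directive: that would drop early events from the intervention arm only.
4. **IV.A.1, VI.B.2 and VI.B.3.** Reconcile when the document is handed over relative to the baseline assessment.
5. **Optional, supportive only.** Compare all randomised patients on admissions from day 31 to month 12. This needs admission dates, which the variable list (VI.A.2) does not mention: it names the number, duration and type of stays. The PMSI might supply them. Patients still in hospital on day 31 must be handled identically in both arms, and there may be several, since section I.B reports an average of 61 days in hospital without consent.

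Items 1 to 4 cost wording only and need no further patients or data, but the stated power becomes less favourable. Item 5 depends on obtaining the dates.
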